### Secondary outcomes

i.WHODAS total score, and each category score (cognition, mobility, self-care, interpersonal relationships, life activities and participation in society) will be summarised by intervention group at baseline, 30 days, 12 weeks and 12 months using mean (standard deviation) or median (interquartile range) depending on the normality of data.ii.Disability free survival will be assessed by identifying whether the patient has a WHODAS score less than 25% at 1-year post surgery, and will be compared between treatment groups using logistic regression. A multivariate analysis may be performed adjusting for clinically prognostic factors, as specified for the primary endpoint.iii.The Clavien-Dindo complication score is an ordinal variable with classification grades I, II, IIIa, IIIb, IVa, IVb, V. The wilcoxon-mann-whitney test will be used to compare between groups. If appropriate, ordinal logistic regression will be used to perform an analysis adjusted for important prognostic variables. The CCI score provides a measure of overall morbidity over the whole period following an intervention, which is reflected on a scale from 0 (no complication) to 100 (death). Data will be checked for Normality and summarised using mean (SD) or median (IQR) as appropriate. If the scores are normally distributed, a t-test will be used to compare groups, and linear regression modelling may be considered in order to adjust for baseline characteristics. For non-normal data, we will check whether logistic transformation improves normality. If not, the wilcoxon-mann-whitney test will be used. The proportion of patients with post-operative morbidity according to POMS will be summarised in each of the nine domains by intervention group/day. Due to the repeated nature of the data, mixed modelling will also be considered.iv.The EQ 5D subscales and overall Health scale will be tabulated at each timepoint (baseline, pre-surgery, week-12 and 12-months post-surgery). Linear mixed modelling will be performed with overall health scale as the outcome variable, and intervention group and baseline health scale as explanatory variables to investigate the effect of intervention considering all timepoints. This will be repeated for the EORTC-QLQ-C30 global health score, and mixed effects ordered logistic regression will be considered for analysis of subscales.

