### Study objectives

Primary objective: investigate whether a multimodal exercise, and psychological support prehabilitation programme, performed in a community-based setting prior to major cancer surgery, (± neoadjuvant cancer treatments) will result in a clinically significant difference (1-day reduction) in post-operative in-hospital length of stay) when compared to a control group.

Secondary objectives: investigate whether the WesFit programme performed prior to major cancer surgery ± neoadjuvant cancer treatments:
i.Improves disability free survival as measured by World Health Organisation (WHO)
Disability Adjusted Survival v2.0
ii.Improves post-operative morbidity
^
44
^ as measured by post-operative morbidity score (POMS) and Clavien-Dindo-Demartines (CD)
^
45
^/comprehensive complication index (CCI) scores
^
46
^
iii.Improves health related QoL as measured by EQ-5D-5L
^
47
^ and EORTC-QLQ-C30.
^
48
^

Exploratory objectives include:
i.Improve overall survival and disease-free at one-year post-surgeryii.Improve selected cardiopulmonary exercise test (CEPT) physiological variablesiii.Improve long-term physical activity behaviouriv.Demonstrate cost effectiveness determined by health economics analysisv.Improve radiological markers of body compositionvi.Improve radiological tumour regression grade (TRG)vii.Improve pathological tumour regression grade (yTRG)viii.Improve psychological outcomes including confidence to self-manage illness, anxiety and depression.ix.Improve body composition measured by computer tomography and bioelectrical impedance analysesx.Improve nutritional and micronutrient status measured by micronutrient blood analysis

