## Secondary outcomes

i.World Health Organisation Disability Adjusted Survival 2.0 (WHODAS 2.0) - The 36 item WHODAS 2.0 questionnaire will be completed at baseline, prior to surgery, day-30, week-12 and 12-months following date of surgery.ii.Post-operative morbidity will be determined by the post-operative morbidity survey (POMS),
^
54
^ the highest in-hospital morbidity achieved according to the Clavien-Dindo-Demartines (CD) score
^
45
^ and the comprehensive complication index (CCI) score.
^
46
^ Patients’ POMS will be characterised on day 3, 5, 7 and 15, while patient remains hospitalised. The POMS 18-item survey will be used to address nine domains of postoperative morbidity (pulmonary, infectious, renal, gastrointestinal, cardiovascular, neurological, wound complication, haematological and pain). On day of discharge, patient’s surgical complications (if any) will be graded using the CD classification of surgical complications This classification is used to assess overall hospital morbidity following surgical procedures. Patients are graded as 0 (no complications) or Grade I-V based on the level of complication, including the number of organ system involvement. Grade V is defined as death of a patient. A record of the CCI – an update of the CD classification will also be collected.iii.Health related QoL will be assessed using the EQ-5D-5L
^
46
^ and the EORTC-QLQ-C30.
^
47
^ EQ-5D-5L is a standardised measure of health status which provides a simple, generic measure of health for clinical and economic appraisal. There are 5 domains (mobility, self-care, usual activities, pain/discomfort, anxiety/depression) each with 5 levels of health. It also includes a visual analogue scale which asks the respondent to rate their health from 0 (worst imaginable) to 100 (best imaginable health). Cancer specific, health-related QoL will be measured using the EORTC-QLQ-C30. This EORTC-QLQ-C30 measures physical, role, emotional, social and cognitive functioning, as well as global QoL and three symptoms; fatigue, pain and nausea/vomiting. For all scales scores range from 0-100. For global and functional scales higher scores reflect favorable QoL, whereas higher symptom scales score indicate more symptoms.

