### Primary outcome

We will summarise, by group, any patients who were randomised, but did not have surgery, and reasons (i.e. death or withdrawal). We will also summarise by group the time between randomisation and surgery. Competing-risks survival regression will be used to model length of hospital stay. This allows for the fact that the participant may die in hospital, thus preventing the occurrence of the event of interest (discharge from hospital). As the time between randomisation and surgery will vary between participants, this will be included in the model. A multivariate model analysis will also be performed adjusting for clinically prognostic factors including age, gender, tumour type, T-stage and neoadjuvant treatment (yes/no). As a secondary analysis, we will perform the above including an interaction term in the model in order to test whether the effect of exercise differs according to whether psychological support is provided or not, although it is recognised that the power to detect any significant interactions in this number of patients will be low.

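### Disability-free survival is defined by a 1-year WHODAS score alone, and the protocol does not say how patients who died before 1 year are classified

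*Protocol article*

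**What the plan says.** Disability-free survival is the first-listed secondary objective (Study objectives) and appears again in the Conclusion. Its working definition is in the Statistical analysis plan, Secondary outcomes, item ii: "Disability free survival will be assessed by identifying whether the patient has a WHODAS score less than 25% at 1-year post surgery". The result "will be compared between treatment groups using logistic regression". Neither sentence mentions death.

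On covariates, the same item adds: "A multivariate analysis may be performed adjusting for clinically prognostic factors, as specified for the primary endpoint". The list it points to, under Primary outcome in the analysis section, is open and does not name baseline WHODAS. The score is nevertheless collected (Outcome measures, Secondary outcomes): "The 36 item WHODAS 2.0 questionnaire will be completed at baseline, prior to surgery, day-30, week-12 and 12-months following date of surgery".

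For EQ-5D, item iv first lists the timepoints to be tabulated, with baseline among them. It then specifies a linear mixed model with the overall health scale as outcome and "intervention group and baseline health scale as explanatory variables to investigate the effect of intervention considering all timepoints". The same model is to be repeated for the QLQ-C30 global score.

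**The concern.** How death is classified is part of the definition of any endpoint called survival. Here the only input to the rule is a questionnaire score, which a patient who has died cannot supply. The text therefore admits at least two analyses that answer different questions. One is restricted to survivors, a group formed after randomisation that the intervention may itself affect. The other treats any absent score as failure and so mixes death with non-response. If the choice is made after the data are seen, the estimate for a leading secondary endpoint can depend on it.

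Two lesser points sit beside this. Baseline WHODAS is available but is not named in a model where it could add power. The EQ-5D wording also leaves open whether baseline is an outcome row as well as a covariate.

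**Working it through.** **No figure to reproduce.** The protocol gives no rate, power or sample size for disability-free survival or for EQ-5D. The check is one of text, with illustrations on assumed inputs.

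**Step 1: where death is placed, outcome by outcome.**

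| Outcome | Place of death in the text |
|---|---|
| Length of stay (analysis section, Primary outcome) | Competing risk: "This allows for the fact that the participant may die in hospital, thus preventing the occurrence of the event of interest" |
| Clavien-Dindo (Outcome measures, Secondary outcomes) | Grade V |
| CCI (analysis section, Secondary outcomes) | Score of 100 |
| Overall survival at 1 year (Exploratory outcomes) | Death is the event |
| Disability-free survival (analysis section, Secondary outcomes) | Not stated |

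**Step 2: effect of the unstated choice.** Let d be the proportion dead by 1 year and q the proportion of survivors with WHODAS below 25%, with every survivor answering.

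- Deaths left out: success proportion = q.
- Deaths counted as failures: success proportion p = (1 − d) × q.
- Odds ratio = [p₁/(1 − p₁)] / [p₀/(1 − p₀)].

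Assume q = 0.70 in both groups and d between 5% and 15%. Leaving deaths out then gives an odds ratio of 1.00 on every line below.

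| d₀ vs d₁ | p₀ vs p₁ with death as failure | Odds ratio |
|---|---|---|
| 5% vs 5% | 66.5% vs 66.5% | 1.00 |
| 10% vs 10% | 63.0% vs 63.0% | 1.00 |
| 10% vs 6% | 63.0% vs 65.8% | 1.130 |
| 15% vs 10% | 59.5% vs 63.0% | 1.159 |
| 6% vs 10% | 65.8% vs 63.0% | 0.885 |

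Worked line: 0.90 × 0.70 = 0.630 and 0.94 × 0.70 = 0.658. The odds are 0.630/0.370 = 1.703 and 0.658/0.342 = 1.924, with ratio 1.130.

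A second assumed case gives a similar size. With q = 0.75 and deaths of 12% vs 8%, the proportions are 0.88 × 0.75 = 66% and 0.92 × 0.75 = 69%. The odds ratio is (0.69/0.31)/(0.66/0.34) = 1.15, against 1.00 with deaths left out.

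**Step 3: every absent score counted as failure.** If a proportion m of survivors does not answer, the success proportion becomes (1 − d)(1 − m)q. A difference in m between groups then moves the odds ratio even when d and q are equal. That movement reflects questionnaire return and neither disability nor survival.

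**Step 4: EQ-5D, if baseline were also an outcome row.** With complete data and no group-by-time term, the group coefficient is that from regressing each patient's mean score on group and baseline. With four rows, that mean is (baseline + 3 × post-baseline mean)/4. The baseline part is absorbed by the baseline covariate, so the group coefficient is exactly 3/4 of the one from post-baseline rows only. A constant 5-point effect becomes 3.75. A simulation (200 runs, N = 1248, SD 20, correlation 0.5) gave 3.74 with standard error 0.55, against 4.99 with standard error 0.73. The ratio of estimate to standard error is 6.8 in both, so the test is unaffected and only the reported size shrinks.

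**The case against.** The strongest reply is that the definition asks a yes/no question of each patient, and a patient who has died does not have a score below 25%. Together with the endpoint's name, that makes death as failure a natural inference. This stands in part. A reader might infer that the logistic regression necessarily drops deaths, but the text does not say so. The rule is undefined; it is not an explicit exclusion. The same literal reading, however, also fails every living patient without a questionnaire, so it does not rescue the definition.

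A second reply is that missing-data handling belongs in a statistical analysis plan that is not shown here, and that overall survival is reported separately. The method for missing scores can indeed be left there. The place of death is different: it is part of the endpoint, the article chose to state the definition, and it placed death explicitly for other outcomes. A separate exploratory survival outcome does not complete this one.

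On baseline WHODAS, a reader might infer that it is excluded. The documents do not support that. The adjustment is optional and the factor list is open: "adjusting for clinically prognostic factors including age, gender, tumour type, T-stage and neoadjuvant treatment (yes/no"). Leaving out a baseline covariate in a randomised comparison does not bias it.

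On EQ-5D, a reader might infer that the model uses baseline twice. The list containing baseline belongs to the tabulation sentence, and the model sentence names baseline only as an explanatory variable. Post-baseline outcomes are the more ordinary reading, so this is an ambiguity and not an error.

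**Conclusion.** The point on deaths holds: the protocol defines disability-free survival by a score alone and gives patients who died no stated class. Under the assumed inputs in Step 2, the choice moves the odds ratio from 1.00 to between about 0.885 and 1.16 for mortality differences of 4 to 5 points. It makes no difference when mortality is equal. The mortality and disability rates are assumptions, so these figures show scale and do not predict the trial's result.

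Naming baseline WHODAS is an improvement at no cost in data. Its omission costs power and leaves the comparison valid; adjustment would also change the odds ratio from marginal to conditional. The EQ-5D and QLQ-C30 wording needs only clarification. On its less likely reading, with four timepoints and no group-by-time term, the estimate falls to three quarters with the test unchanged.

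**What to change.** - Define success as being alive with a WHODAS score below 25% at 12 months after surgery. Count death by 12 months as failure. Treat a missing score in a patient known to be alive as missing data, with the method set out in the statistical analysis plan.
- Name baseline WHODAS as a covariate in the logistic regression for this endpoint.
- In the EQ-5D and QLQ-C30 mixed models, replace the reference to all timepoints with all post-baseline timepoints, so that baseline is a covariate and not also an outcome row.

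The cost is wording only. Baseline WHODAS is already collected, and 1-year vital status is needed for the overall survival outcome. The change should be made before anyone sees outcome data by group.

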## Estimation of sample size

From previous studies, the median length of stay in the control group is estimated to be 7 days. To detect a clinically meaningful difference of a (significance level to detect a hazard ratio of 1.17 when the control group median in-patient time is 7 days) 1 day reduction in LOS with 85% power, alpha = 0.05, a sample size of 1560 participants will need to be recruited over 3 years, with a one year follow-up period. The sample size allows for a 20% drop-out.

Sample size calculations for 2×2 designs are based on the two main comparisons (i.e. exercise vs. no exercise and psychological support vs. no support). The trial sample size is the larger of these 2 comparisons, so in this case, the sample size calculation is powered on the psychological support comparison. The sample size calculation assumes that there is no interaction between the interventions.

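### The quality-of-life mixed models give one coefficient averaged over pre-surgery, week 12 and 12 months, so they cannot separate a pre-operative gain from an effect on recovery

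*Protocol article*

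**What the plan says.** Item iv of Secondary outcomes, under Statistical analysis plan in the Protocol article, says that the EQ-5D subscales and overall health scale "will be tabulated at each timepoint (baseline, pre-surgery, week-12 and 12-months post-surgery"). It then specifies a linear mixed model "with overall health scale as the outcome variable, and intervention group and baseline health scale as explanatory variables". The stated purpose is "to investigate the effect of intervention considering all timepoints". For the second instrument: "This will be repeated for the EORTC-QLQ-C30 global health score".

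The model sentence names no visit effect, no group-by-visit term, no contrast at a given visit and no principal quality-of-life timepoint. Study objectives (secondary objective iii) reads "Improves health related QoL as measured by EQ-5D-5L" and the EORTC-QLQ-C30, also without a timepoint.

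**The concern.** The three follow-up values do not measure the same thing. The pre-surgery score is taken at the end of prehabilitation, before the operation. Week 12 and 12 months describe recovery from it. Exercise sessions and weekly counselling are delivered before surgery, so an effect that differs before and after the operation is plausible.

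Followed as written, the model assumes a single effect common to all three visits. Its one estimate and test cannot show whether patients felt better while waiting for surgery, recovered better, or both. Effects of opposite sign can offset each other.

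A smaller, separate issue is that no visit effect is named. If mean scores differ between visits and the arms are observed in different proportions at those visits, part of the visit difference passes into the group coefficient.

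**Working it through.** **Inputs from the document.** Total sample size 1560 with 20% drop-out allowed (Estimation of sample size): 1560 × 0.8 = 1248 patients, or 624 per level of one factor under 1:1:1:1 allocation. The health scale runs from 0 to 100. The follow-up visits are pre-surgery, week 12 and 12 months.

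**Assumptions, not in the document.** SD 20; correlation 0.5 between any two visits, baseline included; two-sided 5% test; the illustrative effects, visit means and missingness below. The plan states no figure for this analysis, so there is none to reproduce.

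**Step 1: what the coefficient estimates.** With complete data and a random intercept, the three visits carry equal weight:

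coefficient = (d_pre + d_wk12 + d_12m) / 3

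These weights do not depend on the SD or the correlation.

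| True effects (pre, week 12, 12 months) | Coefficient |
|---|---|
| (6, 0, 0) | 2.0 |
| (0, 6, 0) | 2.0 |
| (0, 0, 6) | 2.0 |
| (−6, 3, 3) | 0.0 |

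With equal missingness in both arms (95%, 85% and 80% observed), weight moves towards pre-surgery: (6, 0, 0) gives 2.24 and (0, 0, 6) gives 1.81.

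**Step 2: precision.** Conditional on baseline, the variance is 400 × (1 − 0.25) = 300 and the covariance between visits is 400 × (0.5 − 0.25) = 100.

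- One visit: SE = 2√(300/1248) = 0.98
- Three-visit mean: SE = 2√[((300 + 2×100)/3)/1248] = 0.73
- Mean of week 12 and 12 months: SE = 2√[((300 + 100)/2)/1248] = 0.80

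**Step 3: an effect before surgery only.** A 5-point gain before surgery and none afterwards gives 5/3 = 1.67 with complete data. For SD 18 to 22 and correlation 0.3 to 0.6, this is significant in 52% to 76% of trials. With 5%, 15% and 25% missing at the three visits, equally in both arms, the coefficient is 1.9 and is significant in about 70%.

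**Step 4: an effect at week 12 only, complete data.** The pooled coefficient is compared here with the post-operative average, since that is the contrast proposed to carry a recovery statement.

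| Effect at week 12 | Pooled coefficient (SE 0.73) | Post-operative average (SE 0.80) |
|---|---|---|
| 5 points | 1.67, z = 2.28, power 63% | 2.5, z = 3.1, power about 88% |
| 3 points | 1.0, z = 1.37, power 28% | 1.5, z = 1.9, power about 47% |

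The post-operative average reduces the dilution but does not remove it.

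**Step 5: no visit term, no true effect, unequal missingness.**

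- Visit means 0/−8/−3 relative to pre-surgery; observed 95/75/70% in one arm and 95/90/85% in the other: bias −0.29 without a visit term, 0.00 with one.
- Visit means 72/64/74; 30% v 15% missing at week 12: bias about −0.4 and type I error about 8.5 to 9%; the bias is zero once visit is in the model.

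The sign depends on which arm has more missing data. With complete data or equal missingness, adding a visit main effect alone leaves the group coefficient unchanged. Separating the visits takes the group-by-visit term.

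**The case against.** - **This is one sentence in a condensed article, and the analysis plan is not shown.** That plan may well add visit terms; the sentence also gives no random-effects or covariance structure. This limits how firmly one can say that visit will be left out. It does not dispose of the point, because the article lists the explanatory variables and states the aim, and a reader following it would fit this model.
- **An average over all visits is a legitimate estimand, and it is the one stated.** This stands. The weakness is that this average mixes pre-operative with recovery status and no modelled contrast by visit accompanies it.
- **A reader might infer that a significant result driven by the pre-surgery score would be a false positive against objective iii.** The documents do not support that. The objective names no timepoint and does not exclude a pre-operative gain, and the introduction itself motivates the psychological component by its effect on quality of life and distress. In Step 3 the average effect really is non-zero.
- **A reader might infer that a recovery effect would be hidden.** That is too strong. The EQ-5D tabulation by timepoint would show it descriptively; what is missing is an estimate with a confidence interval.
- **The bias in Step 5 rests on assumed missingness and visit means.** Correct: it is conditional and small on a 0 to 100 scale. The scenarios also remove data from 1248 patients, a number already net of drop-out.

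**Conclusion.** The point holds as a limitation of a secondary analysis. As written, the model yields a coefficient that is roughly the average of three visit effects and cannot distinguish a pre-operative gain from an effect on recovery after surgery. The one-third weights for complete data follow from the model. The power and bias figures depend on the assumed SD, correlation, effects and missingness and serve only as illustrations.

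The absence of an effect by visit carries the point. The absence of a visit main effect is secondary and matters only if missingness differs between arms, with a bias of about 0.3 to 0.4 points in the examples. Nothing here contradicts another part of the document or shows a stated figure to be wrong.

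**What to change.** In item iv, for both the EQ-5D health scale and the EORTC-QLQ-C30 global score, fit visit as a categorical fixed effect and each treatment factor by visit, alongside the baseline score. Report the estimated effect with its confidence interval at pre-surgery, week 12 and 12 months. The all-visit average may stay as a stated summary. Rest any statement about quality of life after surgery on a pre-specified post-operative contrast, for example the average of week 12 and 12 months, and report pre-surgery separately.

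The cost is a change of wording, with no new data. If the effect is truly constant, the post-operative average is less precise than the three-visit average: 0.80 v 0.73 points, about 10% larger. It still dilutes an effect confined to week 12. The separate visit contrasts are several secondary results and need cautious interpretation for multiplicity.
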